#### Exclusion criteria

Patients’ exclusion criteria will be (1) meet of very high-risk ASCVD diagnostic criteria (diagnostic criteria is determined according to 2020 Chinese expert consensus on lipid management of very high-risk atherosclerotic cardiovascular disease patients); (2) one or more of the following complications: heart failure, ventricular tachycardia, second to third-degree atrioventricular block, uncontrolled atrial tachycardia (including atrial flutter, atrial fibrillation, etc.), mural thrombus, cardiac aneurysm, dysfunction or rupture of papillary muscle, severe sinus bradycardia (heart rate < 50 beats/minute), sinus arrest, etc.; (3) history of cardiac arrest; (4) acute non-cardiogenic complications: such as infections, kidney failure, hyperthyroidism, etc.; (5) severe cardiovascular conditions: moderate to severe valvular stenosis, hypertrophic cardiomyopathy, other forms of ventricular outflow tract stenosis, acute myocarditis, pericarditis, active endocarditis, suspected or known aneurysm rupture, acute pulmonary embolism, or pulmonary infarction; and (6) vulnerable populations, including patients with mental disorders, critical illness, age < 18 years old, pregnancy, students or subordinate of principal investigators, employees of the research institute, etc. This trial does not exclude any other concurrent therapies or interventions.

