### Eligibility criteria {10}

#### Inclusion criteria

Patients’ inclusion criteria will be (1) age from 18 to 80 years old; (2) meet of ASCVD diagnostic criteria, including the history of acute coronary syndrome (ACS), myocardial infarction (MI), stable or unstable angina, transient ischemic attack, surgical history of coronary or peripheral vascular reconstructions, etc.; (3) currently taking statins by prescription; (4) no difficulty in using smartphones, basic Chinese reading and writing skills, basic calculation skills; and (5) acceptance of the terms and conditions of the study and signature of the informed consent form.

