#### Relevant concomitant care permitted or prohibited during the trial {11d}

Both the intervention group and the control group will receive standard pharmacological treatments.

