#### Outcomes {12}

Outcomes will be collected at baseline and again at 1, 3, and 6 months during the intervention period.

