### Primary outcome measure

*LDL-C level*. The primary endpoint will be the mean change in LDL-C level [time Frame: from randomization (day 0) to V5 (week 24) for a total of 6 months of treatment]. Per guideline, the LDL-C level has been validated as a primary measurement for the clinical efficacy of the treatments [3].

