### Assignment of interventions: blinding

#### Who will be blinded {17a}

Participants and investigators will be aware of the intervention that has been assigned to them in this open-label trial. Because of the nature of the patient-reported outcome measures, not all outcome evaluations will be blinded. During the analysis, the statistician will be blinded to the allocation.

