### Data collection and management

#### Plans for assessment and collection of outcomes {18a}

Data will be collected utilizing EDC in each site. Data collection takes place at four points: baseline, 1, 3, and 6 months. Collected data will be stored in the form of an electronic case report form. The clinical research coordinator (CRC) will complete the electronic case report form. The investigators will be informed of any changes made by CRC and system/edit check automatically done by the system. Authorized investigators will be permitted to access the study computers and evaluate the data throughout the study.

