#### Confidentiality {27}

Personal information will be collected, shared, and maintained following ICH GCP. Before the start of the research, the principal investigator authorizes the investigators and study nurses the rights to the data set. All participants need to sign the informed consent form for the data to be collected. A randomized number is generated to track each patient. All data will be stored on a secure database (EDC). Only authorized researchers have access to the data set. Authorized researchers only have access to the data collected by themselves. Review of data collected by other researchers is not permitted.

This trial data will not be shared to enable international prospective meta-analyses.

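### Lipid-drug changes after randomisation are left open in an open-label trial with visible LDL-C, and the stated analysis would neither show nor address an imbalance between arms

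*Protocol article*

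**What the plan says.** All places are in the protocol article.

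- **Inclusion criteria.** On lipid therapy, entry requires only that the patient is "currently taking statins by prescription". No time on treatment and no unchanged regimen is stated.
- **Exclusion criteria, last sentence.** "This trial does not exclude any other concurrent therapies or interventions".
- **Relevant concomitant care {11d}.** "Both the intervention group and the control group will receive standard pharmacological treatments". Nothing is said about changes during follow-up.
- **Primary outcome measure.** "The primary endpoint will be the mean change in LDL-C level", from randomisation to week 24.
- **Outcomes {12}.** "Outcomes will be collected at baseline and again at 1, 3, and 6 months during the intervention period".
- **Who will be blinded {17a}.** "Participants and investigators will be aware of the intervention that has been assigned to them in this open-label trial". Only the statistician is blinded.
- **Plans for assessment and collection of outcomes {18a}.** "Authorized investigators will be permitted to access the study computers and evaluate the data throughout the study". Confidentiality {27} narrows this: "Authorized researchers only have access to the data collected by themselves". Investigators can therefore still see the LDL-C of their own patients.
- **Statistical methods {20a}.** The endpoints are tested with a paired-samples t-test, and no covariate is named.
- **Additional analysis {20b}.** The section states that there will be none.

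**The concern.** The primary endpoint is the quantity that lipid-lowering drugs act on most directly, and the trial means to credit a week-24 difference to a CBT lifestyle programme. Randomisation balances what patients bring to day 0. It does not balance prescribing decisions made afterwards by people who know the arm and have seen two interim LDL-C values.

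The bias could run either way. If more control patients have therapy intensified because their LDL-C stays high, a real CBT effect is hidden. If more CBT patients do, an effect appears that CBT did not cause. With an unadjusted test and no further analysis planned, the report would not show which had happened, or whether anything had.

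**Working it through.** **1. Do the conditions for bias coincide?** Four are needed, and the text supplies each:

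- Drug changes are possible: Exclusion criteria and {11d} set no limit.
- The arm is known: {17a}.
- LDL-C is visible before the endpoint: {12}, {18a} and {27}, at months 1 and 3.
- The analysis does not look at drug changes: {20a} and {20b}.

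**2. The plan's own figure.** Sample size {14} gives 122 per group, 80% power, one-sided 0.05 and an expected 20% reduction. No SD is given, so 122 can only be back-solved:

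- Standardised effect = √[2 × (1.645 + 0.842)² / 122] = 0.318.
- If 20% is read as a between-arm difference of 20 percentage points (an assumption), SD = 20 / 0.318 = 62.8 points.

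**3. Size of a drug-driven shift (assumed inputs).** Shift = arm difference in the share intensified × extra fall per intensified patient, in points of percent change:

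- 0.10 × 20 = 2
- 0.10 × 30 = 3
- 0.20 × 20 = 4
- 0.20 × 30 = 6

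The range is 2 to 6 points.

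**4. What such a shift does to a between-arm test.** SE = SD × √(2/122), which is 3.84, 5.12 and 8.04 for SDs of 30, 40 and 62.8. SDs of 30 and 40 are assumptions.

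- *More intensification in the CBT arm, no true CBT effect.* P(reject) = Φ(shift/SE − 1.645), nominally 5%.
- *More intensification in controls, true effect 20 points.* Power = Φ((20 − shift)/SE − 1.645).

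| SD | False-positive rate at shift 2 / 4 / 6 | Power at shift 2 / 4 / 6 |
|---|---|---|
| 30 | 13% / 27% / 47% | 99.9% / 99% / 98% |
| 40 | 11% / 19% / 32% | 97% / 93% / 86% |
| 62.8 | 8% / 13% / 18% | 72% / 64% / 54% |

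A smaller SD makes a false positive more likely. A larger SD makes masking more damaging.

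**5. Time on statin at entry.** This is fixed before randomisation, so it adds variance to a between-arm comparison without shifting it on average. Assume a share p of recent starters who each fall a further 35 points. Then variance = 62.8² + p(1 − p) × 35²:

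- p = 0.1: SD 63.7, power 79%
- p = 0.2: SD 64.3, power 78%
- p = 0.3: SD 64.8, power 78%

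The loss from 80% is 1 to 2 points.

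**The case against.** **Drug-mediated change is partly the intended effect.** The background targets poor compliance with drug as well as lifestyle treatment, the app prompts medication-taking, and controls are taught rational drug use. Comparing two strategies on top of usual care is a legitimate design. This stands for adherence to an unchanged regimen, which should remain part of the CBT effect. It does not cover prescribing changes that follow from knowing the arm.

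**Standard treatment in both arms limits changes.** This stands in part. The open rule closes a list of entry criteria and is not a licence to vary drugs at will, and the article does not say that the investigators themselves prescribe. But standard treatment is not defined as a fixed regimen, and nothing states how a change is handled.

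**Drug recording and covariates are eCRF or SAP detail.** A reader might infer that no two-arm record of lipid drugs exists, because the outcomes list has none and the app's self-tracking serves only the CBT arm. The documents do not support that: an eCRF exists and its fields are not listed. The analysis limb does not rest on silence, because {20b} positively rules out further analysis.

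**Stronger readings about recent statin starters.**

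- A reader might infer that they bias the arm difference. They do not, since randomisation balances them on average. The named paired t-test would count their fall as change within an arm, but that is a fault of the test and a separate matter.
- A reader might also infer a drop in power to 74%, 70% or 67%, by assuming an SD of 25 points and holding the starting power at 80%. Those two assumptions conflict with the plan. With 122 per group and a 20-point difference, SD 25 gives power above 99.99%. It matches 80% only for a difference of about 8 points, which the plan does not state.
- Whether a patient with a very recent acute event could enter cannot be settled, because the very-high-risk exclusion refers to criteria that the article does not reproduce.

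**Conclusion.** The point holds for lipid-drug changes after randomisation. The protocol leaves them open, those who know the arm also have interim LDL-C, and the stated analysis neither reports nor handles them. The week-24 difference could be biased in either direction. The 2 to 6 point size, set against a planned 20%, is an illustration; the documents give no rate of drug change, no drug effect and no SD. The error rates also depend on reading 20% as a between-arm difference and on a between-arm test, which the superiority design and the primary hypothesis call for. Nothing shows that such an imbalance has occurred. Varying time on statin at entry is a minor loss of precision. The point should be acted on, but it does not undermine the design.

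**What to change.** Amend {20a} and {20b} before the allocation is opened to the statistician:

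1. **Primary comparison.** Compare week-24 LDL-C change between arms, adjusted for baseline LDL-C and for lipid regimen started or changed shortly before randomisation (yes/no, with the window defined in advance). Do not use changes after randomisation as a covariate, since they may themselves depend on the arm.
2. **Reporting.** Tabulate lipid-therapy changes after randomisation by arm, with timing and direction.
3. **One supportive analysis.** Prespecify a change of lipid therapy after randomisation as an intercurrent event and state how later LDL-C values are treated. Improved adherence to an unchanged regimen is not such an event and stays in the CBT effect.
4. **Data.** Confirm that the eCRF holds lipid drug, dose and change dates in both arms. If it does not, complete them from prescription records.

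The cost is some data retrieval and one extra analysis. Trial status reports recruitment complete in January 2022 (the Recruitment section expects it to run until 2023), so retrieval may have to be retrospective. Prescription records can supply drugs and dates but not self-reported adherence. No dose, treatment rule or entry criterion needs to change.

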### Who will take informed consent? {26a}

Researchers will perform an initial eligibility screening and collect written informed consent. Written informed consent will be collected prior to baseline assessment.

### Additional consent provisions for collection and use of participant data and biological specimens {26b}

If the data collection is not included in the initial informed consent process for the main clinical trial, each participant in the ancillary study must sign a consent form. This trial does not involve collecting biological specimens for storage.

### Interventions

#### Explanation for the choice of comparators {6b}

A control intervention—conventional lifestyle intervention—will be provided to help compare the effects of CBT in ASCVD patients. The control group will receive patient education delivered with oral communications given by healthcare providers. Patient education including disease-related knowledge, lifestyle guidance, complication prevention, rational drug use, and other contents will also be delivered to the control group. Patient education will be delivered only during each follow-up. Both the intervention group and the control group will receive standard pharmacological treatments.

#### Intervention description {11a}

CBT for ASCVD lifestyle interventions will be delivered by WeChat MiniApp: “CBT ASCVD” (developed by Hangzhou Kang Sheng Health Consulting CO., LTD). This includes 3 sections which are further divided into 6 sessions. The contents are designed and reviewed by cardiologists and psychiatrists from Sir Run Run Shaw Hospital, Zhejiang University, Hangzhou, Zhejiang, China. Participants will study according to a learning schedule which is divided into a strong intervention period (1–2 months) and a regular intervention period (4–6 months) (see Fig. 1).

**Fig. 1 Fig1:**
[figure not shown]
Participants’ learning schedule

#### Criteria for discontinuing or modifying allocated interventions {11b}

Discontinuation from the treatment program will be considered in the following conditions. Participants will not be considered to have dropped out of the experiment at this point, and they will be eligible to receive protocol assessments unless they withdraw their consent for assessments (as described below):If the participant wishes to stop the protocol treatment;If the participant is unable to continue the protocol treatment due to adverse events;When the investigator believes that the risk of continuing the protocol treatment outweighs the benefit for any reason;When the investigator believes that continuing the protocol treatment is not appropriate for any other reason.

#### Strategies to improve adherence to interventions {11c}

Participants in the intervention group will log in to the WeChat MiniApp to complete the intervention sessions according to the schedule. “CBT ASCVD” will track the completion of each session. To improve adherence, the participants will receive positive and constructive feedback through the “clock-in” feature in the “CBT ASCVD” app. Participants will be able to “clock in” from the dashboard to routinely track if they exercise, take medications, and eat healthy.

#### Relevant concomitant care permitted or prohibited during the trial {11d}

Both the intervention group and the control group will receive standard pharmacological treatments.

#### Provisions for post-trial care {30}

Considering the nature of mobile-based patient education, it is unlikely to cause harm to the participants. In case any risk of harm is identified, the principal investigator will intervene to minimize the potential harm. If any harm is identified, the research team will provide them with appropriate compensation if necessary.

#### Outcomes {12}

Outcomes will be collected at baseline and again at 1, 3, and 6 months during the intervention period.

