### Statistical methods

#### Statistical methods for primary and secondary outcomes {20a}

Categorical variables will be expressed in numerical values with their respective percentages and compared using the chi-squared test at baseline. Continuous variables will be expressed as mean ± SD and compared using the *t*-test. The significance of primary and secondary endpoints will be evaluated with the paired-samples *t*-test. A *p*-value < 0.05 indicates statistical significance. All data will be analyzed with the SPSS.

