#### Methods in analysis to handle protocol non-adherence and any statistical methods to handle missing data {20c}

All patients who have received CBT for at least 4 weeks will be included in the full analysis set (FAS). Depending on the time investigated, the per-protocol (PP) analysis set will be made up of patients who complete the 6-month follow-up examinations. The FAS will be used as the basis for the primary analysis. If there is a discrepancy of greater than 10% between the FAS and PP samples, the analysis will be repeated for the PP analysis set. The safety population will include patients in the FAS. Unless otherwise noted, all analysis will be done in both the FAS and PP analysis sets.

There will be no replacement or imputation of missing values. All analysis will be based solely on observed cases. Patients who are loss to follow-up will be considered to have dropped out of therapy. Only the PP patients will be used in a sensitivity analysis to test the impact of this assumption.

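### The primary analysis excludes every patient without a week-24 LDL-C, even when months 1 and 3 were measured, so loss that depends on early response and differs by arm can bias the result in either direction

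*Protocol article*

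**What the plan says.** Four statements in the protocol article together fix the primary analysis.

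- **Outcomes {12}:** "Outcomes will be collected at baseline and again at 1, 3, and 6 months during the intervention period". Plans for assessment and collection of outcomes {18a} gives the same four time points.
- **Primary outcome measure:** the endpoint is the mean change in LDL-C "from randomization (day 0) to V5 (week 24) for a total of 6 months of treatment".
- **Statistical methods {20a}:** "The significance of primary and secondary endpoints will be evaluated with the paired-samples *t*-test".
- **Non-adherence and missing data {20c}:** "There will be no replacement or imputation of missing values", and "All analysis will be based solely on observed cases".

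Section {20c} bases the primary analysis on the full analysis set (FAS), which it defines by at least four weeks of CBT. The sensitivity analysis for loss to follow-up is confined to the per-protocol set, made up of patients who complete the 6-month examinations. Section {20b} plans no further analysis. Sample size {14} allows for up to 20% loss in both groups.

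**The concern.** A paired test needs both members of the pair. With observed cases only and no imputation, a patient who attends at months 1 and 3 and then leaves is dropped, although two post-baseline LDL-C values are in the database. Those values show how the patient was responding before leaving, which is the information needed to judge whether the leavers differ from those who stay.

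The arms could plausibly lose patients for different reasons. The trial is open-label. CBT patients work through scheduled app sessions, while controls receive education only at follow-up visits. If the leavers in one arm are selected on early response and those in the other are not, the remaining patients are no longer comparable as randomised, and the primary result carries that difference.

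This is not a detail left to the analysis plan. The article itself fixes the paired test, the observed-case rule and the ban on imputation.

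**Working it through.** **1. The plan's own sample size.** Inputs from Sample size {14}: 122 per group, 80% power, one-sided 0.05, up to 20% loss, target 150 per group.

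- Inflation: 122 / (1 − 0.20) = 152.5, so 153 per group against 150 stated. The stated figure is reproduced to within 3%.
- No SD is given, so 122 cannot be derived forwards. Solved backwards, the standardised effect is (1.645 + 0.842) × √(2/122) = 0.318, or about 0.32 SD.

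**2. How many patients are affected.** At the maximum loss, 0.20 × 150 = 30 per arm, or 60 of 300, have no week-24 pair. That leaves 120 per arm. Power for a between-arm comparison at 0.318 SD is then 79.4% one-sided, against 80% planned. Power is almost kept, so the question is bias.

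**3. Size of the bias.** The article gives no dropout pattern and no LDL-C correlations, so these are assumptions:

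- 150 per arm (or very large arms), true week-24 effect 0.32 SD, and 20% loss after month 3 unless stated.
- Selective loss means that the log-odds of leaving rise by 1 per SD of poor month-3 change.
- Visit correlations are constant 0.5, constant 0.7, or 0.7 per 3 months with decay. Ranges in the table run over these three.

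The simulated comparison is between arms, on change from day 0 to week 24 in patients with both values.

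| Loss pattern | Week-24 observed cases (SD) |
|---|---|
| Random in both arms | 0.32 |
| Same selection in both arms | 0.32 |
| CBT poor responders leave, control loss random | 0.39-0.43 |
| As above, log-odds 0.5 | 0.36-0.38 |
| As above, 10% loss | 0.35-0.38 |
| Controls selected at half the CBT strength | 0.35-0.37 |
| Control poor responders leave, CBT loss random | 0.21-0.25 |
| CBT good responders leave, control loss random | 0.21-0.26 |

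In relative terms the extremes are 0.43/0.32 = 1.34 and 0.21/0.32 = 0.66, about a third in either direction.

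In the pattern where CBT poor responders leave, adjusting completers for baseline still gives 0.36-0.40, while using months 1 and 3 returns 0.31-0.32. With no true effect, the same pattern produces a spurious benefit of 0.06-0.11 SD, and using months 1 and 3 returns about 0.

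A separate simulation used stronger selection (log-odds 1.5) and changes correlated 0.4, 0.6 or 0.8 between visits. The observed-case estimate was 0.41-0.49 when poor CBT responders left and about 0.14-0.23 when good ones left. Using months 1 and 3 again returned 0.31-0.32.

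**4. Whether the planned sensitivity analysis would show it.** The per-protocol set consists of 6-month completers. These are essentially the patients who already have a week-24 pair, so the comparison sets nearly the same patients against themselves.

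**5. Precision.** Under random loss, using months 1 and 3 has relative efficiency 1.02-1.05 against a baseline-adjusted completer analysis.

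**The case against.** **Stopping the app is not leaving the trial.** Section {11b} keeps patients who stop treatment eligible for assessments unless they withdraw consent for them, and {18b} provides for telephone contact when data are missing. This stands. A reader might infer that CBT patients who abandon the app drop out of the week-24 estimate, but the article does not say so. The risk applies to patients truly lost to follow-up, for whom {14} still allows up to 20%.

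**The planned test is within-patient.** The figures above describe a between-arm comparison, which {20a} does not state for the endpoints. This also stands, and it limits what the figures show. A within-arm paired test is exposed too: losing CBT poor responders overstates that arm's change whatever happens among controls.

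**The pattern is chosen.** A reader might infer that the CBT effect will be overstated by 22-34%. That needs the full 20% loss, all after month 3, selective in the CBT arm only, at log-odds 1. Nothing in the article supports this pattern over one giving no bias or understatement.

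**The model's success is built in.** Loss was made to depend on an observed month-3 value. If it depends on the unseen week-24 change instead, the estimate using months 1 and 3 is about 0.41-0.43, itself roughly 30% too large. It would be wrong to say that the earlier visits remove the bias whatever its cause.

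**A single-time-point endpoint is legitimate, and the early values are not wasted.** Both are true. The abstract lists group measurements at each visit, and the secondary outcomes include the LDL coefficient of variation. The point concerns only how the primary result treats patients without a week-24 value.

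**Conclusion.** The concern holds in conditional form. The stated rules exclude from the primary result any patient without a week-24 LDL-C, whatever was measured earlier, and the planned sensitivity analysis cannot reveal selective loss. If loss relates to earlier LDL-C response and differs by arm, a between-arm effect of 0.32 SD may be estimated at roughly 0.21 to 0.43 SD. The direction is unknown in advance. The range rests on the assumed 20% loss, selection strength and visit correlations; weaker selection or less loss narrows it, and stronger selection widens it. The article supports neither a definite overstatement nor a definite size. It does support calling this an avoidable exposure of the primary result, worth correcting because the data needed are already scheduled.

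**What to change.** In {20a} and {20c}, make the primary analysis a between-arm, likelihood-based repeated-measures model for LDL-C at months 1, 3 and 6. Include arm, visit, arm-by-visit, baseline LDL-C and baseline-by-visit, with unstructured covariance. Take the week-24 arm contrast as the single primary result.

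Fit it to all randomised patients of both arms with at least one post-baseline LDL-C. This is essential: read literally, the FAS rule of at least four weeks of CBT admits no controls and removes early CBT stoppers, so a model fitted to that set would not give a randomised contrast.

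Replace the completers-only sensitivity analysis with one that allows data to be not missing at random, for example by shifting the week-24 values of patients lost in each arm over a stated range.

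**Cost:** changes of wording and one mixed-model procedure, available in SPSS. No new data or visits are needed. Endpoint and time point stay as they are, and because the model uses observed values only it respects the no-imputation rule. The downside is reliance on missing at random, which is weaker than the present completer assumption but does not cover loss driven by the unobserved week-24 value. Trial status reports recruitment complete, so the change should be fixed in writing before the blinded statistician learns the allocation.
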